5. Who provided	**Physiotherapists**: Local NHS senior physiotherapists will facilitate group discussions during each weekly education session. As trained by the study team, they will encourage participants to share experiences and ask questions related to that week’s topic or the management of their hip pain in general. The physiotherapists will also ensure adherence to the intervention by reminding participants to complete their activity diaries in between sessions. **Fitness Instructor**: a qualified and experienced fitness instructor from the local leisure centre will deliver the cycling session each week. The fitness instructors have experience of leading cycling sessions with mixed ability groups and have helped to design the content of each weeks’ session alongside the study team.
6. How	The intervention will be delivered face-to-face in a group setting. After each weeks’ session, participants will be sent a link (via email or text message) to that weeks’ education and cycling session as well as the home exercise programme so that they can be reviewed in between sessions in participants’ own time. A short report detailing changes in assessment scores will be sent to participants following treatment.
7. Where	Intervention will be delivered at a suitable local leisure centre, equipped with space to deliver the education session and an appropriately equipped cycling studio that has space for up to 15 participants to take part in a single cycling session
8. When and how much	The CHAIN intervention is an 8-weeks cycling and education programme where participants will attend a one-hour education and exercise session on a weekly basis at a local leisure centre. It is not necessary for the intervention to be delivered in consecutive weeks and a short pause in delivery of the programme will be possible in the case of local facilities having to close, i.e., due to public holidays or other situations out of the study team’s control. However, if a participant misses a planned course, there will not be an opportunity to provide a catch-up session and the participant will be marked as absent from the session. Dosage received for each participant will be calculated based on sessions attended and length of those cycling sessions along with the recommended cycling intensity.
9. Tailoring	Static cycling is an accessible form of exercise which can be tailored to all levels of ability and fitness within a group setting.
10. Modifications	N/A

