### Follow-up (visit 4, visit 5)

There will be two follow up assessments, the first within 2 weeks of the end of the CHAIN intervention (or end of 8 weeks treatment period for the control arm) (Visit 4) and the second (Visit 5) occurring approximately 3 months after the post-treatment visit. Visit 4 will be undertaken by trained, qualified physiotherapists and will consist of the same physical and functional assessments performed at Visit 2, completion of patient questionnaires as well as a review of participants’ activity diaries and a feedback questionnaire for those participants that were randomised to the CHAIN intervention; Visit 5 consists of 5 patient questionnaires (Hip Disability and Osteoarthritis Outcome Score (HOOS); Patient Specific Functional Scale (PSFS); Patient Activation Measure (PAM); EQ-5D-5 L; and resource use) sent to participants by email or post. Participants will be contacted by text/telephone/email to help ensure completion and return of questionnaires. Where this is difficult to achieve, we will prioritise collection of the primary outcome at Visit 4. The data to be collected at each of these follow-up appointments are summarised in Table 1.

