### Adverse events

Hip OA is a non-life-threatening condition typified by on-going progression of symptoms and deterioration of function. From the time the participant signs the consent form until the day the participant has completed their post-treatment assessment (Visit 4), the only adverse events recorded will be those for which participants seek advice from a health care professional, such as an unplanned visit to a General Practitioner for an acute condition. Participants will be asked at the start of each CHAIN session or physiotherapy session whether they have had any adverse events, and they will be asked again at the assessment post-treatment.

Based on our feasibility study [18] as well as a case study of a participant with a number of co-morbidities [26], the intervention is deemed low risk. Therefore, we are not expecting any serious adverse events.

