### Sample size calculation

The sample size calculation is based on the primary outcome measure, the physical function score from the HOOS function scale at Visit 4. This has identical items to the Western Ontario and McMaster Universities Osteoarthritis Index (WOMAC) function scale [31], with total score transformed to a percentage. Mean primary outcome will be compared between the intervention and control arms using baseline function score as a covariate. The literature mostly uses the WOMAC function score, so parameters for the sample size calculation are based on that, though we indicate the equivalent HOOS score where relevant. We will assume a correlation between pre and post exercise outcomes of 0.6 and take this into account in the calculation [32]. This is a conservative estimate based on (a) our feasibility study data and Wallis *et al’s* study [33], for which the lower limits of the 95% confidence interval were 0.75 and 0.69 respectively, and (b) Bennell et al.’s research [34] that assumed a value of 0.6 for their sample size calculation. This will reduce the required sample size by a factor of 0.64. To allow for any clustering effects resulting from the group delivery of the CHAIN intervention, we have inflated the variance of this arm by a factor of 1.22, assuming a cluster size of 12 and intra-cluster correlation coefficient of 0.02 [35]. Using a 5% two-sided significance test, an effect size (average of minimum clinically important difference found previously [36, 37]) of 5 points on WOMAC (equivalent to 7.4% on HOOS) and standard deviation (average taken from previous literature [36–39] and the feasibility study [18]) of 13 on WOMAC (equivalent to 19.1 on HOOS) a sample size of 102 per arm would be required for 90% power. Allowing for a withdrawal and/or incomplete primary outcome data rate of 20% (for example [40]) the recruitment target will be increased to 256 (9 clusters of size 14–15 in the intervention arm). The sample size calculation was partly conducted using NQuery Advisor software (San Diego, USA).

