### Statistical analysis

Prior to completing data collection, a detailed Statistical Analysis Plan will be written and approved by the Trial Steering Committee. Participants’ data will be analysed in the group they were randomised to, and we will attempt to collect outcome data on all participants unless they requested to be withdrawn from the study (‘intention to treat’ analysis). Analysis and initial write-up will be blinded to treatment groups and reported according to the Consolidated Standards of Reporting Trials. Baseline characteristics of the sample in each arm of the trial (e.g., demographics, body composition, etc.) will be summarised using descriptive methods. The primary outcome of the function component of HOOS measured at Visit 4 will be compared between trial arms using a multi-level/mixed model approach, considering baseline function and CHAIN group (cluster).

We will conduct a per protocol analysis where participants will be excluded from the analysis if (a) there was a protocol violation (including swapping treatment arms) or (b) adherence to exercise was poor (e.g., attendance at less than 87.5% of classes i.e. less than 7 classes) or adherence to physiotherapy was poor in the control arm (e.g. attendance at less than 100% of sessions i.e. participant must attend all physiotherapy sessions recommended by therapist).

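### No adverse-event enquiry is described for participants who stop sessions and then miss Visit 4, so harms that lead to drop-out may be under-recorded

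*Protocol article*

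**What the plan says.** The Adverse events section of the protocol article fixes both the times of enquiry and the threshold for recording.

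- During treatment: "Participants will be asked at the start of each CHAIN session or physiotherapy session whether they have had any adverse events".
- After treatment: "they will be asked again at the assessment post-treatment".
- Threshold: "the only adverse events recorded will be those for which participants seek advice from a health care professional".
- Window: from signed consent "until the day the participant has completed their post-treatment assessment (Visit 4").

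Table 1 matches this. Adverse events are marked at Visit 2, during treatment and at Visit 4, but not at Visit 5.

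Three other sections bear on people who stop attending.

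- Table 3 (item 8) says of a missed CHAIN session that "the participant will be marked as absent from the session". It describes no contact about the reason.
- Follow-up (visit 4, visit 5) says "Participants will be contacted by text/telephone/email to help ensure completion and return of questionnaires", and gives priority to the primary outcome at Visit 4 when collection proves difficult. Visit 5 is done entirely by email or post.
- Statistical analysis says "we will attempt to collect outcome data on all participants unless they requested to be withdrawn from the study".

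**The concern.** After baseline, every enquiry the article describes needs the participant to take part in a session (which in the control arm may be by telephone) or to attend Visit 4. Someone who has a hip flare, consults a GP, gives up the programme and does not come to Visit 4 meets the recording threshold. No later point is described at which that person would be asked.

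This loss is unlikely to be random with respect to harm. In a trial of an exercise programme, an event caused by the exercise is one of the more plausible reasons for stopping. If such stopping is commoner in one arm, the comparison of harms tilts in that arm's favour.

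The article deems CHAIN low risk on the basis of a feasibility study and a case study, and gives low risk as one reason for having the Trial Steering Committee act as data monitoring committee. The trial's own adverse-event data are the natural test of that premise. They would be weakest for the people who tolerated the programme least.

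**Working it through.** **Step 1: who is asked, on the stated scheme.**

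| Participant | Asked at sessions | Asked at Visit 4 | Gap |
|---|---|---|---|
| Attends sessions and Visit 4 | Yes | Yes | None |
| Stops sessions, attends Visit 4 | Up to the last session attended | Yes | None at the end |
| Stops sessions, misses Visit 4 | Up to the last session attended | No | Everything after the last session attended |

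Only the third row is affected. Visit 5 may still reach such a person, but Table 1 schedules no adverse-event collection there. The Resource Use Questionnaire covers health-care contacts, but it is listed as health economic data and as the source for analgesia use. It is not an adverse-event enquiry.

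**Step 2: an upper planning figure for that group.** The article states no figure for adverse events, so the only guide is the loss allowance in the sample size section: "Allowing for a withdrawal and/or incomplete primary outcome data rate of 20" per cent. I reproduced the calculation first. The inputs are a difference of 5 and SD of 13 on WOMAC, two-sided 5%, 90% power, a factor of 0.64 for baseline correlation, and variance inflation of 1.22 in the CHAIN arm only.

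- Normal approximation: n per arm = 0.64 × (1 + 1.22) × [13 × (1.960 + 1.282)/5]² = 100.9.
- Noncentral t: 102 per arm gives power 0.9003, matching the stated 102.
- Inflation: 102/0.80 = 127.5, rounded up to 128 per arm, or 256 in total, as stated.
- Planned loss: 0.20 × 256 = 51.2, or 25.6 per arm. That is about 26 of 128 (20.3%).

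**Step 3: what a gap of given size could do.** The event rates here are my assumptions and are not in the article. Take 128 per arm with m not asked at the end, and no event recorded for them earlier. Let 10% of the others have a recordable event, and let a proportion q of the m have had one.

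- Recorded events = 0.10 × (128 − m).
- True proportion = [0.10 × (128 − m) + q × m]/128.

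| m not asked | Recorded, out of all 128 | True, q = 10% | True, q = 50% | True, q = 100% |
|---|---|---|---|---|
| 6 | 12.2/128 = 9.5% | 10.0% | 15.2/128 = 11.9% | 18.2/128 = 14.2% |
| 13 | 11.5/128 = 9.0% | 10.0% | 18.0/128 = 14.1% | 24.5/128 = 19.1% |
| 26 | 10.2/128 = 8.0% | 10.0% | 23.2/128 = 18.1% | 36.2/128 = 28.3% |

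**Step 4: can the analysis repair it?** If only those asked form the denominator, the recorded proportion is 10% in every row. That is right when q = 10% and too low whenever q is higher. If the unasked differ because they were harmed, changing the denominator does not recover their events. The information has to be collected.

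**The case against.** The strongest reply is that stopping treatment is not leaving follow-up. Outcome data are sought on everyone except those who ask to be withdrawn. Visit 4 is timed from the treatment period, not from attendance, and adverse events are asked about there. So a reader who infers that people who stop because of harm are never asked goes further than the article allows. They are asked if they come to Visit 4, and they were asked at each session before stopping. This stands, and it confines the point to those who do neither.

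A reader might also infer that unasked participants will be counted as event-free. The article gives no such rule and no adverse-event denominator. Denominators and listings commonly belong to the analysis plan, so that inference is unsupported.

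On size, the 20% covers withdrawal and incomplete primary outcome data for any reason. A shortfall of about 20 percentage points would need all 26 to have had an event that no earlier session picked up. That is an arithmetical limit, not an expectation.

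The recording window might be read as open-ended for someone who never completes Visit 4. Table 1 dates that visit to within two weeks after the 8-week period, and an open window would not in itself cause under-recording.

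Finally, this article condenses a full protocol (v4.1) that may contain a withdrawal or safety procedure. Nor does it say that events learned of by other routes go unrecorded. Both are fair cautions. But the article does not merely stay silent: it sets out when the question is asked, Table 1 repeats it, and the chasing contact is described as being for questionnaires. If the full protocol already closes the gap, the remedy is to say so.

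**Conclusion.** The point holds in a limited form. On the scheme as stated, a participant who stops sessions and does not attend Visit 4 is not asked about events since the last session attended, although the trial already has remote means of reaching that person. Harms may be under-recorded in this group, and possibly unequally by arm.

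The size cannot be determined from the article. About 26 of 128 per arm is an upper planning figure for the number affected, and the true number could be far smaller. With an assumed 10% event rate among those asked, 6 unasked would put 9.5% recorded against 10.0% to 14.2% true. With 26 unasked it would be 8.0% against 10.0% to 28.3%, the top of that range being extreme.

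The conclusion rests on two assumptions: that stopping is sometimes a consequence of an event, and that no procedure outside the article already covers these participants. It is a cheap improvement to data collection. It does not touch the primary outcome analysis.

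**What to change.** In the Adverse events section, provide that every participant in either arm who misses Visit 4, and has not refused further contact, is asked two things through the existing text, telephone or email contact:

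1. whether they have had an adverse event, under the same care-seeking definition, up to the date Visit 4 was due;
2. if they stopped attending, why.

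The Follow-up section should name this as a purpose of that contact, alongside the return of questionnaires.

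The cost is a small amendment, a few more calls and a slightly higher recorded event count. There is one real drawback. The Trial status section expects recruitment to finish by May 2023, so a change now would make ascertainment differ between earlier and later cohorts. The change would apply equally to both arms, and it should be noted when adverse events are reported.

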### Sample size calculation

The sample size calculation is based on the primary outcome measure, the physical function score from the HOOS function scale at Visit 4. This has identical items to the Western Ontario and McMaster Universities Osteoarthritis Index (WOMAC) function scale [31], with total score transformed to a percentage. Mean primary outcome will be compared between the intervention and control arms using baseline function score as a covariate. The literature mostly uses the WOMAC function score, so parameters for the sample size calculation are based on that, though we indicate the equivalent HOOS score where relevant. We will assume a correlation between pre and post exercise outcomes of 0.6 and take this into account in the calculation [32]. This is a conservative estimate based on (a) our feasibility study data and Wallis *et al’s* study [33], for which the lower limits of the 95% confidence interval were 0.75 and 0.69 respectively, and (b) Bennell et al.’s research [34] that assumed a value of 0.6 for their sample size calculation. This will reduce the required sample size by a factor of 0.64. To allow for any clustering effects resulting from the group delivery of the CHAIN intervention, we have inflated the variance of this arm by a factor of 1.22, assuming a cluster size of 12 and intra-cluster correlation coefficient of 0.02 [35]. Using a 5% two-sided significance test, an effect size (average of minimum clinically important difference found previously [36, 37]) of 5 points on WOMAC (equivalent to 7.4% on HOOS) and standard deviation (average taken from previous literature [36–39] and the feasibility study [18]) of 13 on WOMAC (equivalent to 19.1 on HOOS) a sample size of 102 per arm would be required for 90% power. Allowing for a withdrawal and/or incomplete primary outcome data rate of 20% (for example [40]) the recruitment target will be increased to 256 (9 clusters of size 14–15 in the intervention arm). The sample size calculation was partly conducted using NQuery Advisor software (San Diego, USA).

### Statistical analysis

Prior to completing data collection, a detailed Statistical Analysis Plan will be written and approved by the Trial Steering Committee. Participants’ data will be analysed in the group they were randomised to, and we will attempt to collect outcome data on all participants unless they requested to be withdrawn from the study (‘intention to treat’ analysis). Analysis and initial write-up will be blinded to treatment groups and reported according to the Consolidated Standards of Reporting Trials. Baseline characteristics of the sample in each arm of the trial (e.g., demographics, body composition, etc.) will be summarised using descriptive methods. The primary outcome of the function component of HOOS measured at Visit 4 will be compared between trial arms using a multi-level/mixed model approach, considering baseline function and CHAIN group (cluster).

We will conduct a per protocol analysis where participants will be excluded from the analysis if (a) there was a protocol violation (including swapping treatment arms) or (b) adherence to exercise was poor (e.g., attendance at less than 87.5% of classes i.e. less than 7 classes) or adherence to physiotherapy was poor in the control arm (e.g. attendance at less than 100% of sessions i.e. participant must attend all physiotherapy sessions recommended by therapist).

### Economic evaluation

The economic evaluation will use data collected within the trial to establish the resources required to provide the intervention, estimate its cost, and provide a full cost-effectiveness analysis (CEA). In order to comply with NICE guidance [41] the economic evaluation will take a primary perspective of the NHS/Personal Social Services, i.e., it will include costs borne by the NHS and statutory social care services only. The impact on cost-effectiveness results of taking participant and societal perspectives, which incorporate costs to patients, their families and wider society, will be explored in sensitivity analyses.

Cost and outcome data will be synthesised to present incremental cost-effectiveness ratios (ICERs) - the incremental cost per unit of additional outcome - for the primary outcome (cost per unit change on the HOOS measure) and the primary economic endpoint of policy relevance (cost per QALY).

Intervention resource requirements and costs (e.g., staff time, venue hire, educational materials, travel, communication, consumables) will be collected at an individual participant level, using case report forms. Resource use data (including primary and secondary healthcare, social care, and participant and carer-related resource use) will be collected at Visits 1/2, 4 and 5, using a self-report Resource Use Questionnaire. This questionnaire will draw on measures used with similar populations in the Database of Instruments for Resource Use Management (DIRUM) repository [42, 43], alongside current practice and recent methodological developments [44] and be honed to this specific population through discussion with the study Patient Advisory Group. QALYs will be derived from EQ-5D-5 L trial data, collected at Visits 1/2, 4 and 5. In line with NICE recommendations [45], EQ-5D-5 L data will be mapped to the EQ-5D-3 L UK tariff [46] using the approved ‘cross-walk’ algorithm [47]. These mapped values will be used to estimate QALYs through application of standard area-under-the-curve methods [48] using Visit 1/2, 4 and 5 assessments. Incremental costs and incremental Quality-adjusted life years (QALYs) over 24 weeks will be used to estimate the cost-per-QALY of CHAIN versus usual physiotherapy care.

We will follow the internationally recognised Consolidated Health Economic Evaluation Reporting Standards (CHEERS) guidelines for reporting cost-effectiveness studies [49]. Descriptive statistics will be used to summarise costs (by type of service) and QALYs. Regression analyses will be used to adjust for any systematic differences between intervention and control arms at baseline that have not been accounted for by randomisation. If required, we will use multiple imputation to correct for bias that may result from data missing at random [50]. Sensitivity analyses will explore uncertainty, and a clear, policy-relevant presentation of findings will be provided. All analyses will be conducted in line with the statistical analysis plan.

A cost-consequences analysis will also present key costs and outcomes in a disaggregated, tabular format [51, 52]. This will enable assessment of the component parts of the intervention, health/social care and patient resource use and costs of care, and multiple outcomes, for the intervention and control arms.

### Patient and participant involvement

A public and participant involvement forum, comprising six people who had undertaken the pilot CHAIN programme has informed this protocol, providing feedback on the study design and documentation, the design of the intervention, the main outcome of interest and how the data would be disseminated [53]. The forum was held in April 2014 at the leisure centre where the pilot programme took place and its findings informed the investigators’ decision to increase the number of sessions in the programme from six to eight weeks, allow further time for questions, and continue to include an exercise diary. The trial Patient Advisory Group (PAG) provided feedback on the Participant Information Sheet (PIS) and the resource use questionnaire. They will provide on-going advice to the Trial Management Group on management of the research, further participant-facing documentation and participant questionnaires, analysis of results and dissemination of findings. The PAG will also identify a member of their group to represent them on the Trial Steering Committee.

